##### HIV vulnerability

Although the effect of the intervention on HIV risk will be assessed in the primary analysis, we will also analyze the effect of the intervention on specific behaviours. Several self-reported binary measures will be used to determine the effect of the intervention on HIV vulnerability in the previous 6-month period, including injection drug use in the past 6 months, high-frequency (daily or more) drug use, needle sharing, and participation in sex work. These measures will be ascertained from Cedar Project questionnaires collected every 6 months as part of the main Cedar Project cohort. HIV vulnerability will be assessed at baseline, 6 months, and 1 year.

##### Resilience

Resilience, or the ability to cope with adversity, will be characterized by using the Connor-Davidson Resilience Scale (CD-RISC). The creators of the scale broadly define resilience as “personal qualities that enable one to thrive in the face of adversity” [42]. The CD-RISC scale measures resilience via 25 items on a five-point scale with scores ranging between 0 and 100, with higher scores indicating greater resilience. Resilience will be assessed at baseline, 6 months, and 1 year.

##### Psychological distress

The Symptom Checklist-90-R (SCL-90-R) is a 90-item self-reported symptom inventory that measures the severity of nine dimensions of psychological distress in the past 3 months scored on a five-point Likert scale (from ‘not at all’ to ‘extremely’). Participants’ SCL-90-R scores will be transformed into an average Global Severity Index, providing a single average measure that profiles overall degree of psychological distress [43]. Psychological distress will be assessed at baseline, 6 months, and 1 year.

##### Access to drug-related services

Self-reported access to drug-related services, including opioid substitution therapy, needle exchange, safe injection facility, and drug treatment, in the previous 6-month period, will be ascertained from the main Cedar Project questionnaire. Proportions of participants reporting access to these services will be compared in the intervention and control groups. We will also determine whether there are differences among treated and control groups in terms of proportion of people who tried to quit in the previous 6-month period. Access to drug-related services will be assessed at baseline, 6 months, and 1 year.

##### Connection to culture

Connection to Indigenous culture has been hypothesized as a key protective factor for young Indigenous people who use drugs. It will be assessed by using two dichotomous variables that measure cultural activity in the prior 6-month period: (1) self-reported participation in traditional ceremonies (including potlatch, feast, fast, burning ceremony, washing ceremony, naming ceremony, big/smoke house, rites of passage, smudge, dances, or any other traditional Indigenous ceremony) and (2) frequency living by traditional culture (never/rarely versus often/always). These variables were defined by [name] (Cree, Métis) and [name] (Lheidli T’enneh) who are Indigenous Elders, traditional knowledge keepers, and members of the Cedar Project Partnership.

### Sample size

Considering current follow-up rates, we are likely able to reach and recruit at least 200 participants for participation in both arms of the Cedar Project WelTel mHealth study. As mentioned previously, the primary objective is HIV risk, measured by using an HIV propensity score evaluated at 6 months. On the basis of a 1:1 allocation ratio, a significance level of 0.05 (one-sided) and 80 % power, it is estimated that we require 78 participants in each study arm. This computation assumes a standardized mean effect size (using Cohen’s d) of 0.40. Assuming attrition rates of approximately 20 %, we intend to over-enroll, resulting in a target of 200 participants overall (100 in each arm). Sample size was calculated by using the pwr package in R, software version 3.2.1.

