## Methods and design

### Study design

The Cedar Project WelTel mHealth study is a two-site, two-arm, parallel group, open, stratified Zelen pre-randomized controlled trial to measure the effect of a culturally safe, two-way supportive text-message intervention to reduce HIV vulnerability among young Indigenous people who use illicit drugs in a community-based setting (ClinicalTrials.gov identifier NCT02437123). Participants will be pre-randomized to two groups—either the mHealth intervention or standard care—at a 1:1 allocation ratio.

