#### Intervention group

To ensure that we reach our target sample, initial randomization will be slightly unbalanced to accommodate refusals to participate or difficulty locating participants. A total of 140 participants (70 from each site) will be randomly allocated to receive the invitation to participate in the intervention arm of the mHealth study. This will allow for an estimated 20 participants per site who cannot be reached or who decline to participate. Cedar staff will invite and enroll participants from this list to join the study until enrollment reaches 50 at each study site. Three attempts will be made to invite participants in the intervention arm into the study, including during regular visits to the research offices, phone, email, word of mouth, and street outreach.

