### Statistical analysis

The analysis and reporting of the results will follow the CONSORT (Consolidated Standards of Reporting Trials) guidelines [44]. Descriptive statistics of socio-demographic, historical/lifetime trauma, sex- and drug-related HIV vulnerabilities, and health-related variables will be presented to assess comparability of the intervention and control groups. Mean (standard deviation) or median (quartiles) will be used for continuous variables and count (percentage) for categorical variables. Our primary analysis to evaluate the effect of the mHealth intervention on HIV prevention will be by intention to treat (ITT) for primary and secondary outcomes among all randomly assigned participants according to the study group to which they were originally allocated. Student’s *t* tests and chi-squared tests will be used to determine differences in the mean change in proportions or scores from baseline at 6 months or 1 year between the two study arms. If baseline characteristics are found to be substantially different between the two study arms, we will adjust for these factors by using regression models. In addition, we will conduct a secondary analysis by using a modified ITT approach including only participants who agreed to participate in the intervention making up the intervention group (excluding over-sampled participants who did not receive the intervention). To minimize the risk of bias introduced in our modified ITT analysis, we propose to use complier average causal effect (CACE) analysis [45]. This approach will allow us to retain the initial random assignment by taking into account two subgroups within the group pre-randomized to receive the intervention (those who did and did not actually receive the intervention) and then helping us to identify a similar subgroup of control participants who could have been expected to receive the intervention had it been offered [45]. By comparing expected and observed outcomes in these subgroups, we will obtain a less biased estimate of effect of the intervention [45]. Missing data will be approached by using multiple imputation. An up-to-date version of R statistical software will be used to conduct all analyses [46]. All tests will be two-sided; *P* values of less than 0.10 will be considered significant. We plan to conduct four predetermined exploratory subgroup analyses that may help to tailor the intervention for specific high-need populations, including comparisons by gender, city, injection drug use, and urban versus rural. Statistical methods similar to those described above for whole-group analyses will be conducted for primary and secondary outcomes. All subgroup results will be reported, regardless of significance. Inferences will be hypothesis-generating, given concerns related to multiple comparisons and lower power to detect an effect in subgroups.

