### Limitations

Our decision to over-sample in the intervention arm to adjust for refusals to participate or difficulty locating participants may result in a dilution of the effect of the intervention in ITT analysis. As a result, we have proposed a parallel, modified ITT analysis, which may be affected by selection bias. Diversity of HIV risk among participants (non-homogeneity) may also dilute the detected effect of the intervention. Representativeness of the sample is dependent on representativeness of the Cedar Project cohort study sample overall; however, we have made a considerable attempt to ensure that the sample represents the population under study [12]. As this study involves a package of support that includes mobile phones, two-way text messaging, and support, it is difficult to determine the relative contribution of components of the package to any effect the intervention may have. The qualitative nested studies will help in this regard. Furthermore, we cannot rule out that simultaneous co-interventions could impact our results. As BC’s HIV incidence has been stable for several years and many public health initiatives (including needle exchanges and safe injection sites) are already in place, we feel it is unlikely that new transformative co-interventions will take effect over the study period. However, we will monitor potential co-interventions that could impact study outcomes through our main cohort questionnaires, as well as track major policy and programmatic changes in the Province. Blinding in this study is not possible as assessors have strong relationships with participants. In addition, loss to follow-up may be higher in the comparison group than the intervention group. Cedar Project participants are highly transient and often difficult to track down [41]. Having a mobile phone and consistent airtime will likely make it easier to reach participants receiving the intervention for follow-up visits. Active follow-up with all participants through phone, email, and outreach will help ensure retention and interview appointment attendance. In addition, our measures may not adequately capture complex concepts such as connection to culture and resilience. Finally, the intervention under study is complex and multifaceted. It may be that our proposed outcomes do not adequately capture the impact of the intervention on the lives of participants involved.

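### The stated 80% power makes no allowance for non-uptake and does not describe the primary ITT comparison of 140 invited with 100 controls, of whom at most 100 of the 140 can be treated

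*Protocol article*

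**What the plan says.** All references are to the protocol article.

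- **Sample size** assumes 1:1 allocation, a standardised mean effect of 0.40, a one-sided 0.05 level and 80% power, and concludes that "it is estimated that we require 78 participants in each study arm". With attrition of about 20%, the target becomes 200 enrolled, 100 per arm.
- **Intervention group**: "A total of 140 participants (70 from each site) will be randomly allocated to receive the invitation". The excess is meant to cover an estimated 20 people per site who decline or cannot be reached. Then: "Cedar staff will invite and enroll participants from this list to join the study until enrollment reaches 50 at each study site".
- **Comparison group** allocates 100 cohort members as controls.
- **Statistical analysis** makes ITT the primary analysis, "among all randomly assigned participants according to the study group to which they were originally allocated". Over-sampled people who did not receive the intervention are left out only in a secondary modified ITT analysis, which is supported by a CACE analysis. Tests are two-sided, and P "values of less than 0.10 will be considered significant".
- **Study design** says participants are pre-randomised "at a 1:1 allocation ratio". Participants and Sample size also use 1:1.
- **Limitations** concedes that over-sampling "may result in a dilution of the effect of the intervention in ITT analysis". The Discussion makes a similar remark about refusals.

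**The concern.** The power calculation and the primary analysis refer to different sets of people. Sample size works from equal arms of enrolled participants and allows only for attrition. The primary test uses everyone allocated, and 40 of the 140 in the invited arm cannot be treated under the plan's own enrolment cap. If the assumed effect is one expected in people who get the intervention, averaging over the 140 shrinks it, and the stated 80% is not the power of the primary test.

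This matters when the result is read. The article gives no other power figure. After a null ITT result, a reader would take the trial to have had 80% power against d = 0.40, without knowing whether that holds for the effect in recipients, in the allocated arm, or neither.

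**Working it through.** **Inputs.** d = 0.40, one-sided 0.05, 80% power, about 20% attrition, 78 and then 100 per arm (Sample size); 140 allocated, cap 2 × 50 = 100 enrolled (Intervention group); 100 controls (Comparison group); ITT on all randomised, two-sided 0.10 (Statistical analysis). Two-sided 0.10 has the same upper critical value as one-sided 0.05, so that difference in wording does not affect the results below.

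**1. Reproduce the plan's figure.** Normal approximation: n per arm = 2(1.645 + 0.842)² / 0.40² = 77.3, rounded up to 78. The noncentral t also gives 78, with power 80.0%. Inflation: 78 / 0.80 = 97.5, so 98, rounded to 100 per arm. The 80% therefore belongs to 78 v 78 evaluable. 80 v 80 gives 81%, and 100 v 100 all analysed would give 88%.

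**2. Composition of the primary comparison.** Allocated 140 v 100, a ratio of 1.4:1. Maximum uptake 100/140 = 71.4%. With 20% attrition in both arms: 140 × 0.8 = 112 and 100 × 0.8 = 80.

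**3. Diluted effect.** ITT d = uptake × effect in recipients + (1 − uptake) × effect in non-recipients. With 0.40 in recipients and zero in non-recipients: 0.40 × 100/140 = 0.286.

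**4. Power.** Normal approximation: Φ(d / √(1/n₁ + 1/n₂) − 1.645). For 112 v 80, √(1/112 + 1/80) = 0.1464, so 0.286 / 0.1464 − 1.645 = 0.307, giving 62.1%. The noncentral t values are:

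| Reading of d = 0.40 | ITT d | 112 v 80 (20% attrition) | 140 v 100 (no attrition) |
|---|---|---|---|
| Effect in recipients, none in the other 40 | 0.286 | 61.8% | 70.2% |
| Effect in the allocated arm (ITT) | 0.40 | 85.9% | 91.9% |

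On the second reading the implied effect in recipients, again with none in the others, is 0.40 × 140/100 = 0.56.

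**5. Detectable effect.** For 80% power at 112 v 80, ITT d must be about 0.365, which is 0.365 × 1.4 = about 0.51 in recipients.

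**6. Sensitivity to uptake.** On the recipient reading at 112 v 80, 90 treated gives 54% and 100 gives 62%. Reaching 80% would take between 126 treated (79.0%) and 130 treated (81.1%), well above the cap of 100.

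**The case against.** The strongest objection is that Sample size never says 0.40 is the effect in recipients. If it was meant as the effect in the arm as allocated, power at 112 v 80 is about 86% and the trial is not short of power. This stands, and it makes the 62–70% conditional. Against it, the section's target counts people reached and enrolled, and its only allowance is for attrition. Nor is the implied recipient effect of 0.56 stated anywhere. The recipient reading is the more natural one, but it remains an inference.

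A second objection is that the authors disclose dilution and plan modified ITT and CACE in response. They do. But the caveat is not quantified and is not carried into the power statement. Both analyses are secondary and do not restore power to the primary test, and Limitations itself says the modified ITT may suffer selection bias. The Discussion's expectation of few refusals does not help either, because the cap leaves 40 of the 140 untreated however willing people are.

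Third, Intervention group openly says that the initial randomisation is somewhat unbalanced, and 1:1 can be read as the enrolled target of 100 and 100. That is fair for Sample size. Study design and Participants apply 1:1 to the randomisation itself, so their wording still needs reconciling.

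A reader might infer that the sample size was miscalculated, or that 80% was claimed for 100 v 100. Neither is so: 78 per arm is correct for its inputs, and 100 is the attrition-inflated target. A reader might also assume that the 40 non-enrolled give no outcome data. The documents do not support that, since outcomes come from routine cohort visits.

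**Conclusion.** The point holds as a mismatch between the basis of the sample size and the primary analysis. The stated 80% is correct for 78 v 78 evaluable at d = 0.40 but makes no allowance for non-uptake, while the primary comparison is 140 v 100 with uptake of at most 71%.

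The size depends on what 0.40 means. If it is the effect in recipients, and the 40 non-recipients have no effect, power is about 62% with 20% attrition in both arms and about 70% with none. If it is the ITT effect, power is about 86% at 112 v 80, with d of about 0.56 needed in recipients.

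It would go too far to conclude that the trial simply has 62% power at its own effect size. At an ITT effect of 0.40 it does not, and the documents do not settle which effect was assumed. The ITT analysis remains valid either way; only the power claim attached to it is unsupported.

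**What to change.** Restate Sample size for the planned ITT comparison:

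- allocation 140:100 and uptake of at most 100/140;
- whether 0.40 is the effect in recipients or the ITT effect;
- the resulting power (about 62–70% on the recipient reading, according to attrition) or the detectable effect for 80% power at 112 v 80 (ITT d about 0.365, about 0.51 in recipients);
- the assumptions of no effect in non-recipients and equal attrition in both arms.

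Reconcile the 1:1 wording in Study design, Participants and Sample size with the 140:100 allocation in Intervention group and Comparison group, for example by keeping 1:1 for the enrolled target only.

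The cost is a change of wording and, on the recipient reading, a less favourable stated power. Allocation and analysis stay as they are, and no additional participants or controls are proposed.

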### Statistical analysis

The analysis and reporting of the results will follow the CONSORT (Consolidated Standards of Reporting Trials) guidelines [44]. Descriptive statistics of socio-demographic, historical/lifetime trauma, sex- and drug-related HIV vulnerabilities, and health-related variables will be presented to assess comparability of the intervention and control groups. Mean (standard deviation) or median (quartiles) will be used for continuous variables and count (percentage) for categorical variables. Our primary analysis to evaluate the effect of the mHealth intervention on HIV prevention will be by intention to treat (ITT) for primary and secondary outcomes among all randomly assigned participants according to the study group to which they were originally allocated. Student’s *t* tests and chi-squared tests will be used to determine differences in the mean change in proportions or scores from baseline at 6 months or 1 year between the two study arms. If baseline characteristics are found to be substantially different between the two study arms, we will adjust for these factors by using regression models. In addition, we will conduct a secondary analysis by using a modified ITT approach including only participants who agreed to participate in the intervention making up the intervention group (excluding over-sampled participants who did not receive the intervention). To minimize the risk of bias introduced in our modified ITT analysis, we propose to use complier average causal effect (CACE) analysis [45]. This approach will allow us to retain the initial random assignment by taking into account two subgroups within the group pre-randomized to receive the intervention (those who did and did not actually receive the intervention) and then helping us to identify a similar subgroup of control participants who could have been expected to receive the intervention had it been offered [45]. By comparing expected and observed outcomes in these subgroups, we will obtain a less biased estimate of effect of the intervention [45]. Missing data will be approached by using multiple imputation. An up-to-date version of R statistical software will be used to conduct all analyses [46]. All tests will be two-sided; *P* values of less than 0.10 will be considered significant. We plan to conduct four predetermined exploratory subgroup analyses that may help to tailor the intervention for specific high-need populations, including comparisons by gender, city, injection drug use, and urban versus rural. Statistical methods similar to those described above for whole-group analyses will be conducted for primary and secondary outcomes. All subgroup results will be reported, regardless of significance. Inferences will be hypothesis-generating, given concerns related to multiple comparisons and lower power to detect an effect in subgroups.

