### Outcome measures

#### Primary outcomes

The primary outcome (Table 1) is HIV risk, measured by an HIV propensity score assessed at the 6-month time point. Previous analyses of Cedar Project data with respect to HIV infection have identified several factors as associated with HIV infection, including recent injection drug use, high-frequency drug use, needle sharing, and participation in sex work [12]. Logistic regression of risk factors for prevalent HIV infection at study recruitment will provide coefficients to combine these four risk variables into a single primary outcome measuring propensity for HIV infection. Mean change in HIV propensity score from baseline to 6 months will be used to determine the impact of the intervention on HIV vulnerability.

**Table 1 Tab1:** Outcome measures

Outcome measure	Specific variable	Analysis metric	Hypothesis (intervention > control)	Type	Analysis
Primary					
HIV propensity (6 months)	HIV propensity score	Mean change - HIV propensity score	Decrease in HIV risk	Continuous	T test
Secondary					
HIV propensity (12 months)	HIV propensity score	Mean change - HIV propensity score	Decrease in HIV risk	Continuous	T test
HIV vulnerability	Injection drug use	Mean change - proportion injection	Decrease in injection	Binary	χ^2^ test
	High-frequency injection	Mean change - proportion frequent injection	Decrease in injection frequency	Binary	χ^2^ test
	Needle sharing	Mean change - proportion needle sharing	Decrease in needle sharing	Binary	χ^2^ test
	Participation in sex work	Mean change - proportion sex work	Decrease in sex work	Binary	χ^2^ test
Resilience	Connor-Davidson Resilience Scale (CD-RISC)	Mean change - CD-RISC score	Increase in resilience	Continuous	T test
Psychological distress	Symptom Checklist-90-R (SCL-90-R)	Mean change - SCL-90-R score	Decrease in psychological distress	Continuous	T test
Access to drug-related services	Opioid substitution therapy (OST)	Mean change - proportion accessed OST	Increase in access OST	Binary	χ^2^ test
	Needle exchange (NX)	Mean change - proportion attended NX	Increase in access NX	Binary	χ^2^ test
	Safe injection facility (SIF)	Mean change - proportion visited SIF	Increase in access SIF	Binary	χ^2^ test
	Drug treatment	Mean change - proportion seeking treatment	Increase in seeking treatment	Binary	χ^2^ test
	Tried to quit using drugs	Mean change - proportion trying to quit	Increase in trying to quit	Binary	χ^2^ test

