Connection to culture	Participation in traditional ceremonies	Mean change - proportion participated in traditional ceremony	Increase in access to ceremony	Binary	χ^2^ test
	Frequently living by traditional culture	Mean change - proportion lived by traditional culture	Increase in traditional culture	Binary	χ^2^ test

All variables refer to behaviour in the 6-month period preceding the interview. All variables are measured as mean change in proportion or score from baseline

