#### Secondary outcomes

The potential benefits of the supportive mHealth intervention are broad. As a result, multiple secondary outcomes are of interest. These were selected through consultation with academic and community partners and are part of routine Cedar Project data collection. They fall under five categories: HIV risk, resilience, psychological distress, access to drug-related services, and connection to culture. For all secondary outcomes, the effect of the mHealth intervention will be measured as change in the outcome from baseline to 6 months. Participants with sufficient follow-up time will contribute to analyses of all outcomes at the 1-year time point to determine longer-term effects of the intervention.

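### For the 11 binary secondary outcomes, the chi-squared test named does not match the stated metric of mean change in proportion; a baseline-adjusted comparison would match better and cost only wording

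*Protocol article*

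**What the plan says.** The metric is stated consistently as change. The Secondary outcomes section says that "the effect of the mHealth intervention will be measured as change in the outcome from baseline to 6 months", and the Table 1 footnote says "All variables are measured as mean change in proportion or score from baseline". Each binary row of Table 1 follows this pattern, for example "Mean change - proportion injection", and each names a chi-squared test. There are 11 such rows: four HIV-vulnerability behaviours, five service-related outcomes and two culture outcomes. They are analysed at 6 months and at 1 year.

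The Statistical analysis section repeats the pairing: "chi-squared tests will be used to determine differences in the mean change in proportions or scores from baseline". It does not say which table the test is applied to.

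The section on access to drug-related services describes something different, a plain comparison between arms: "Proportions of participants reporting access to these services will be compared in the intervention and control groups". Regression adjustment appears only as a conditional step: "If baseline characteristics are found to be substantially different between the two study arms, we will adjust for these factors by using regression models".

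**The concern.** A person's change in a yes/no behaviour is -1, 0 or +1, and the stated effect is the between-arm difference in the mean of that score. A Pearson chi-squared test can be set up on these data in two obvious ways, and neither targets that difference directly. A 2x2 table of arm by follow-up status does not use the baseline. A 2x3 table of arm by change category uses the baseline, but asks whether the whole distribution of change differs, in any direction.

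Two analysts could therefore follow the same text and report different p-values for the same outcome. Across 11 outcomes and two time points, and in the subgroup analyses that reuse similar methods, that leaves the results open to choice. It may also give up power that data already collected would supply.

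**Working it through.** **The plan's own figure.** The Sample size section uses d = 0.40 with "a significance level of 0.05 (one-sided) and 80 % power". The normal formula gives n = 2(1.645 + 0.842)²/0.40² = 77.3, so 78; the t-based calculation gives 77.97, also 78. Allowing for 20% attrition, 78/0.80 = 97.5, so 98, which the plan rounds to 100. The figure reproduces. The Statistical analysis section says "All tests will be two-sided" with a 0.10 threshold; a two-sided 0.10 test has the same critical value and also gives 78. No power is stated for any binary outcome.

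**Inputs for the check.** From the article: two-sided 0.10, and 100 per arm less 20% attrition = 80 completers per arm. Assumed, because the article gives none of them: baseline prevalence, effect, and phi, the correlation between a person's baseline and follow-up status.

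**Model.** With baseline proportion p and follow-up proportion q, P(yes at both visits) = pq + phi·√[p(1-p)q(1-q)], and the other cells follow from the margins. Controls stay at p; the intervention arm moves to q. There were 20,000 replicates per scenario. The baseline-adjusted analysis is represented by the Mantel-Haenszel test stratified on baseline status, which stands for baseline-adjusted logistic regression.

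**Power, 80 per arm, p = 0.50, q = 0.35:**

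| phi | chi-squared, follow-up | chi-squared, 3 change categories | Wald/t on mean change | baseline-adjusted | loss, follow-up | loss, categories |
|---|---|---|---|---|---|---|
| 0 | 60.0% | 31.7% | 38.8% | 60.6% | 0.6 | 28.9 |
| 0.2 | 59.9% | 36.7% | 44.2% | 62.3% | 2.4 | 25.6 |
| 0.3 | 60.2% | 40.6% | 49.0% | 64.5% | 4.3 | 23.9 |
| 0.5 | 60.3% | 51.8% | 60.4% | 72.2% | 11.9 | 20.4 |
| 0.7 | 60.2% | 78.9% | 80.8% | 85.9% | 25.7 | 7.0 |

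The usual variance factors, relative to a follow-up-only comparison, explain the pattern: 2(1 - phi) for change and 1 - phi² for baseline adjustment. At phi 0.5 these are 1.00 and 0.75; at phi 0.3 they are 1.40 and 0.91.

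**Other settings.** With p = 0.30, q = 0.15 and phi 0.5, power is 75% (follow-up), 70% (categories) and 85% (adjusted). If all 140 invited and 100 comparison participants are analysed less 20% (112 v 80), p = 0.50, q = 0.35 and phi 0.5 give 67%, 58% and 78%.

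**Size.** With the same transition rates in both arms (prevalence 0.30 or 0.50), the uncorrected tests reject in about 9% to 11% of runs against a nominal 10%. A continuity-corrected 2x2 test rejects in 6% to 7%.

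**Significance without a difference in mean change.** Take 50% at baseline in both arms. One arm has persistence 70% and onset 30%; the other has 90% and 10%.
- First arm: 0.5 × 0.30 = 15% stop and 0.5 × 0.30 = 15% start.
- Second arm: 0.5 × 0.10 = 5% stop and 0.5 × 0.10 = 5% start.

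Mean change is zero in both. With 112 v 80 participants, the 2x3 chi-squared test rejects in about 93% of runs and the baseline-adjusted analysis in about 10%. The transition rates are chosen to show the mechanism, not as a forecast.

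**The case against.** The strongest reply is that this is a gap in wording, not a wrong analysis, and much of it stands.

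- A reader might infer that no chi-squared test can address mean change. That is not so. A 1-df linear-trend or Wald chi-squared test on the -1/0/+1 score does. With 112 v 80, baseline 50%, persistence 65% v 85% and onset 5% v 10%, power was 54% for follow-up status, 61% for three categories, 70% for linear trend and 77% for the baseline-stratified test, all with size near 10%. But the article names no such variant, and the table above shows that testing mean change is still less efficient than adjusting for baseline.
- Under randomisation the expected baseline proportions are equal, so the difference in follow-up proportions has the same expectation as the difference in mean change. A follow-up chi-squared test therefore addresses the same population null, less efficiently. The proposed regression relies on the same equivalence.
- A reader might infer wrong error rates. That would follow from treating baseline and follow-up proportions as independent samples, which nothing in the article proposes and which would be conservative. The two natural readings hold their size when transition rates are equal.
- A reader might infer that a large loss of power is established. On follow-up status it needs phi of about 0.5 or more. The scenario in the first bullet implies phi of about 0.75 in controls and 0.63 in the intervention arm, which is the high end.
- Regression adjustment is already foreseen, and an article may leave table layouts to the analysis plan. But the adjustment depends on an observed imbalance with no threshold, whereas adjusting for a prognostic baseline gains precision whether or not the arms differ. And here the article does fix both the metric and the test, and the two do not fit.

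**Conclusion.** The point holds as a mismatch between metric and test for 11 secondary outcomes, with a cost in efficiency and interpretability. It does not hold as a claim of inflated false positives, nor as a claim that chi-squared methods are unusable.

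Baseline adjustment was at least as powerful as either Pearson reading in every scenario with a real effect, up to simulation error. The gain over follow-up status is negligible at low phi and substantial at high phi; the gain over change categories is 20 points or more up to phi 0.5. These sizes rest on assumed prevalence, effect and phi. Phi may well differ between outcomes as unlike as injecting and trying to quit. The trial stratifies on recent injection, so baseline can be expected to matter at least for that outcome.

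Nothing here touches the primary outcome, its t test or the 78 per arm.

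**What to change.** In the binary rows of Table 1 and in the Statistical analysis section, replace the chi-squared test with a comparison of 6-month (and 1-year) status between arms by regression, adjusted in all cases for baseline status, site and injection stratum. Use logistic regression with a standardised risk difference, or a linear-probability model with robust standard errors where cells are sparse. Report adjusted risk differences with confidence intervals, and give observed change from baseline descriptively. Align the sentence on access to drug-related services with this. For the injection outcome, baseline status and the injection stratum may nearly coincide; say that one of them is dropped if so.

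The cost is wording only: the same data, no extra visits, no change to the sample size, and standard functions in R, which the plan already uses.
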